## **7.2 Recruitment and screening**

### **7.2.1 Recruitment strategies**

Patients will be recruited using the SHCS database. According to the database, it is estimated that >2500 individuals followed at the participating centres in 2014 (out of 8900 participants) are potentially eligible. However, the genotype is not available to screen patients solely on the basis of the SHCS database and the potential number of candidates will be therefore downgraded to 1200. If 15% of the patients agree to participate, the recruitment will be completed within a year.

Possible candidates will be contacted by their attending physician or delegates (e.g. study nurse, study coordinator) and will undergo screening procedures according to the protocol after giving written consent. No advertising is intended at this stage other than information about the protocol (flyer in appendix 2) in the study centers and local HIV/AIDS associations. Participants will not receive financial compensation for participation. Recruitment will continue until the target sample size is reached. In the event of slow or insufficient recruitment, study sites visits will be conducted and human resources allocated. In addition, an international collaboration could be sought in case a rapid recruitment is needed.

### **7.2.2 Feasibility of recruitment**

The prospective research cohort (SHCS) has been already used successfully to plan randomized controlled trials and other clinical trials in the field of HIV in Switzerland, including SNF grants (SNF grant 32003B\_135745). As the SHCS is highly representative of the HIV care and treatment network in Switzerland, with over 75% of all HIV-infected individuals included this cohort in Switzerland (93), we consider that we have an excellent tool to estimate patient recruitment.

All participating SHCS sites agree to recruit patients according to the following table:

| Site | Number of patients |
|-------------|---------------------------|
| Geneva      | 34                        |
| Lausanne    | 24                        |
| Lugano      | 12                        |
| Bern        | 28                        |
| Zürich      | 50                        |
| St Gallen   | 12                        |
| Basel       | 24                        |

## **7.3 Assignment to study groups**

### **7.3.1 Allocation sequence**

Patients will be randomised 1:1:1:1 using randomly-permuted blocks of varying sizes to one of the four study arms (one computer-based randomization list stratified per study center).

### **7.3.2 Concealment mechanism**

Each of the 7 centres will receive the attribution number using a central computer-based randomization system.

### **7.3.3 Implementation**

One allocation sequence stratified per study center will be generated by an independent team who will not be involved in the implementation of the study on sites using a computer-generated sequentially numbered randomization list. Lists will be transferred to the electronic case report form based on a standardized process. The process ensures that lists are stored with restricted access so that only

system administrators have access. Once eligibility criteria are confirmed and when the patient has provided oral written consent to participate in one of the 7 centers enrolled in the trial, the study nurse on site (or the study investigator) will register the patient in the electronic data capture system after which the allocation will be revealed.

## **7.4 Criteria for withdrawal / discontinuation of participants**

Participants will be withdrawn from the trial if:

1. The subject withdraws consent; in this case the patient will continue the antiretroviral treatment with a standard-of-care treatment (cART) and will continue regular follow-up with his/her treating physician;
2. Clinical reasons believed to be life-threatening by the physician, even if not addressed in the toxicity management protocol;
3. Subject is judged by the investigator to be at significant risk of failing to comply with the provisions of the protocol so as to cause harm to self or seriously interfere with the validity of the study result.
4. Study routine procedure must be stopped due to safety concerns.

Withdrawn participants will not be replaced.

Participants in the DTG + FTC dual therapy maintenance arm will discontinue study drugs if (non exhaustive list):

- diagnosed with virological failure defined as plasma HIV-RNA  $\geq 100$  copies/ml on two consecutive occasions;
- become pregnant
- start breastfeeding;
- requiring to use prohibited concomitant medications such as carbamazepine, oxcarbamazepine, phenytoin, phenobarbital, rifampicin or St John's Wort;
- presenting serious adverse events that necessitate to stop dolutegravir and/or emtricitabine;
- reasons related to conceiving and DTG potentially safety issue.

They will still be included in the study, continue their antiretroviral treatment with a standard cART. They can be switched to their previous ARV regimen or to a different one according to the genotypic resistance testing, drug-drug interactions profile and/or clinical evolution, and will complete study procedures until week 48. If the new regimen still fulfills the eligibility criteria the subject can continue the study, otherwise the subject will be withdrawn from the trial. In case of a pregnancy the viral load measurement will be performed once per month accordingly to the EACS guidelines.

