### 7.1 Eligibility criteria

Participants fulfilling all of the following inclusion criteria are eligible for the study:

1. Informed consent as documented by signature
2. Documented HIV-1 infection;
3. Enrolled in the SHCS or receiving care from a medical doctor of the SHCS network;
4.  $\geq 18$  years of age;
5. HIV-RNA  $< 50$  copies/mL at screening and for at least 24 weeks before screening on effective suppressive cART, one blip with less than 200 copies/mL allowed during this period if followed by at least 2 results  $< 50$  copies/mL;
6. On standard cART at the time of inclusion, i.e.:
  - 2 NRTIs + either 1 NNRTI, 1 boosted PI or 1 INSTI;
  - NRTI-sparing triple ARV regimen (e.g. 1 NRTI + 1 NNRTI + 1 INSTI);
  - Dual therapy with protease inhibitor.

Every effort will be made to include women (91) in the same proportion as in the prospective SHCS (28% of HIV-infected individuals included into the SHCS are female; SHCS website demographic data, accessed 20 December 2017).

The presence of any of the following exclusion criteria will lead to exclusion of the participant:

1. HIV-2 infection;
2. Previous ART change for unsatisfactory virological response, i.e. slow initial virological suppression, incomplete suppression or rebound; change for convenience or toxic effect prevention or management allowed.  
*Note: patients with documented genotype(s) presenting only a M184V mutation remain eligible;*
3. Creatinine clearance  $< 50$  mL/min;
4. ASAT or ALAT  $> 2.5$ x upper limit of the norm;
5. Known hypersensitivity, intolerance or allergy to DTG or FTC;
6. Known or suspected non-adherence (defined as  $< 80\%$  adherence, i.e. missed dose  $> 1$ x/week), to current treatment in the last 24 weeks;
7. Concomitant use of drugs that decrease dolutegravir blood concentrations including carbamazepine, oxcarbamazepine, phenytoin, phenobarbital, St John's wort and rifampicin;
8. Women who are pregnant or breast-feeding;
9. a. Presence of any INSTI-resistance. (92).  
b. Non availability of previous routine resistance test, at least for reverse transcriptase and protease genes.  
*Note: Subjects remain eligible in the absence of any previous resistance test only if they are on their first-line antiretroviral regimen;*
10. Evidence of acute or chronic hepatitis B virus infection based on results of serology testing as follows:
  - subjects positive for HBsAg are excluded (corresponding to acute or chronic infection);

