### 8.1.2 Control Intervention (standard/routine/comparator treatment)

Patients in the control intervention will be on fully suppressive antiretroviral regimen.

The control intervention may include several options:

- 2 NRTIs + either 1 NNRTI, 1 boosted PI or 1 INSTI;
- NRTI-sparing triple ARV regimen (e.g. 1 NRTI + 1 NNRTI + 1 INSTI);
- Dual therapy with protease inhibitor (such as PI + NRTI or NNRTI or INSTI).

Within-class antiretroviral switch (such as switch from TDF to TAF) are accepted during the study period only for patients randomized in the continuing cART arm. Other antiretroviral switch are discouraged and sponsor agreement is needed before the switch.

The following regimens will be excluded:

- Two-drug combinations with: 1 NRTI + 1 NNRTI, 1 NRTI + 1 PI without RTV, 1 NRTI + RAL, 2 NRTIs, MVC + RAL (not recommended by European guidelines);
- Triple NRTIs combination (not recommended by European guidelines);
- Dual therapy with DTG other than PI-based dual regimen, such as DTG + NRTI, DTG + NNRTI (simplified regimen already);
- PI monotherapy (simplified regimen already).

Standard monitoring includes a standard 12-weekly routine immunological and safety blood monitoring, including CD4 cell count, lipids and glucose, creatine kinase, renal and hepatic function tests, at affiliated SHCS sites.

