### **8.6 Trial specific preventive measures**

Concomitant medication(s) will be reviewed at baseline, at each visit thereafter and in case HIV-RNA is measured  $\geq 100$  copies/ml. Patients receiving anti-epileptic drugs such as carbamazepine, oxcarbamazepine, phenytoin, phenobarbital, St John's wort, or receiving the antibiotics rifampicin will not be eligible for the study. The concomitant administration of these drugs with dolutegravir decreases the plasma concentration of dolutegravir, and thus increasing the risk of virological failure. Patients on anti-tuberculosis treatment may be eligible at completion of anti-TB drugs. The use of these drugs is part of the exclusion criteria to the study and will be recorded in the screening CRF.

Pregnant women or breastfeeding mothers will not be eligible for the study as triple antiretroviral therapy is standard of care for these conditions. Pregnancy and breastfeeding are part of the exclusion criteria and will be recorded in the CRF.

Women of child-bearing potential will be screened for pregnancy at the screening visit of the study. Those who are found to be pregnant will be excluded from study participation (i.e. screening failure) and referred to an appropriate medical service.

Women of child-bearing potential included into the trial will further undergo urine pregnancy test once every 6 months (i.e. at week 24 and 48 visits). Results of screening and follow-up urine pregnancy tests will be recorded in the study CRF.

Women who become pregnant or start breastfeeding after randomisation will be switched to standard triple cART not containing dolutegravir and will continue the study. They will continue to be monitored for the development of adverse events (AE) or serious adverse events (SAE), and for pregnancy outcome.

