After May 23, 2018, women of child-bearing potential and on dolutegravir are quickly identified by Sponsor-investigator and Study Sites and these women are all informed about the safety signal concerning DTG use in early pregnancy and risk of neural tube defect in infants born to women using DTG in early pregnancy. As communicated on May 25, 2018 to the leading Ethics Committee and to the DSMB (see appendix n° 7 and n° 8 respectively), these women are all asked to sign an information sheet explaining this risk. In case of willingness of pregnancy, they are switched to DTG-free regimen, at study investigator's discretion. In case of non-willingness of a pregnancy, the use of an effective contraceptive method (oral, injectable, implantable contraceptive and intrauterine contraceptive device are considered effective contraceptive methods as well as condom in stable couple and sexual abstinence) is proposed, if not already used by the women. Women of child-bearing potential, on dolutegravir, without willingness of a pregnancy, and refusing to use an effective contraceptive method are proposed to change their ART to a DTG-free regimen. If any of the above procedure is not respected, the sponsor will decide to withdraw the concerned patient from the study.

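### Section 7.4's general switching and withdrawal sentences do not match the pregnancy provisions in Sections 8.6 and 10.1.2

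*Protocol*

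**What the plan says.** **Section 7.4.** The stopping list opens "Participants in the DTG + FTC dual therapy maintenance arm will discontinue study drugs if (non exhaustive list") and has six entries: confirmed virological failure, pregnancy ("become pregnant"), breastfeeding, need for a prohibited co-medication, a serious adverse event that requires stopping, and reasons to do with conceiving and dolutegravir safety. A single paragraph then applies to everyone on the list. It says "They can be switched to their previous ARV regimen or to a different one", guided by genotype, interactions and/or clinical course. It adds that a participant whose new regimen still meets eligibility may continue, and that otherwise the participant is withdrawn. The paragraph closes with a viral-load schedule for pregnancy, so its authors had pregnant participants in mind.

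**Section 8.6.** "Women who become pregnant or start breastfeeding after randomisation will be switched to standard triple cART not containing dolutegravir and will continue the study". For women on dolutegravir who wish to conceive, the text added after the May 2018 signal says: "In case of willingness of pregnancy, they are switched to DTG-free regimen, at study investigator's discretion". Neither statement is limited to one treatment arm.

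**Section 10.1.2.** A pregnancy during the study does not lead to withdrawal.

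**Section 8.1.2.** In the control arm, within-class switches are accepted. For the rest: "Other antiretroviral switch are discouraged and sponsor agreement is needed before the switch".

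**The concern.** The person who stops study drug at a site will look first at Section 7.4, because that is where the stopping criteria stand. For the pregnancy-related stops it offers the previous regimen without restriction and does not refer to Section 8.6. If that regimen contained dolutegravir, a woman could stop DTG + FTC because of a dolutegravir concern and restart the same drug in her old combination. If it was protease-inhibitor dual therapy, she would not be on triple therapy.

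The second issue is whether she stays in the trial. Section 7.4 makes this depend on the new regimen. Sections 8.6 and 10.1.2 do not. The answer affects her safety follow-up and also which HIV-RNA values exist for the primary outcome.

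**Working it through.** The plan gives no figure to reproduce on this point. The check is a comparison of the texts, followed by one small calculation for the withdrawal issue.

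1. **Can a previous regimen contain dolutegravir?** Yes. Inclusion criterion 6 in Section 7.1 allows "2 NRTIs + either 1 NNRTI, 1 boosted PI or 1 INSTI" with no exception for dolutegravir. Sections 3.6 and 8.1.2 exclude dolutegravir dual therapy only where it is not based on a protease inhibitor. Section 3.7 sets apart those participants in the DTG + FTC arm who are new to dolutegravir, which implies that others are not.

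2. **Can a previous regimen be something other than triple therapy?** Yes. The same criterion admits protease-inhibitor dual therapy.

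3. **The provisions side by side**

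| Question | Section 7.4 | Section 8.6 | Section 10.1.2 |
|---|---|---|---|
| Who is covered? | DTG + FTC arm | Women who become pregnant or breastfeed, and women of child-bearing potential on dolutegravir; no arm limit | Any participant who becomes pregnant |
| Next regimen | Previous or different; no dolutegravir exclusion | Pregnant or breastfeeding: triple, dolutegravir-free. Wishing to conceive: dolutegravir-free, at the investigator's discretion | Silent |
| Stay in the trial? | Only if the new regimen meets eligibility | Pregnant or breastfeeding women continue | Pregnancy does not end participation |

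4. **Result for the regimen.** For a woman whose entry regimen contained dolutegravir or was protease-inhibitor dual therapy, one of the two options in Section 7.4 is not allowed by Section 8.6 once she is pregnant or breastfeeding. For a woman who wishes to conceive, the conflict arises only if the old regimen contained dolutegravir.

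5. **Result for staying in the trial.** The rules differ in kind: one is conditional, the others are not. Section 8.6 does have a withdrawal clause of its own, but it is tied to disregard of the conception procedure and not to the eligibility of the regimen. In practice the conflict is narrow, because a triple regimen chosen under Section 8.6 will usually satisfy criterion 6.

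6. **What one withdrawal could do to the primary outcome.** Under Section 11.5, a participant with no HIV-RNA at weeks 36 and 48 counts as a failure. With 92 per arm, one participant counted as a failure instead of a success moves that arm's proportion by 1/92 = 0.0109, or about 1.1 percentage points, against a margin of 12 points. This assumes that she is withdrawn before week 36, has no later value, and would otherwise have stayed suppressed. Per-protocol membership in the DTG + FTC arm hardly depends on the conflict: Section 11.4.1 already excludes those who stop treatment before 47 weeks unless they failed virologically first.

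**The case against.** The strongest reply is that the sections are compatible. Section 7.4 is general and permissive and offers a different regimen as an alternative. Section 8.6 is specific and mandatory. A site that reads both can comply with both, and nothing in Section 7.4 obliges anyone to restart dolutegravir. For the conception-related stop, Section 7.4 itself names dolutegravir safety as the reason, so a return to the drug would make no sense. This reply stands as far as it goes. It rules out the inference that Section 7.4 defeats the safety measure: that would need a site to use Section 7.4 alone and a woman whose earlier regimen contained dolutegravir. It does not remove the missing cross-reference or the differing rules on staying in the trial.

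Three other inferences are tempting but not supported.

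- **That control-arm women on dolutegravir are left out.** The list in Section 7.4 names one arm, but it concerns that arm's study drugs, and Section 8.6 covers both arms. This is at most a gap in Section 7.4. The step in Section 8.1.2 is procedural and may not arise if the replacement is within class. What remains open is whether it applies when Section 8.6 requires the switch.
- **That the size is 4/426 = 0.94% applied to 28% of 184, about 52 women.** The rate in Section 3.2 relates to early-pregnancy use, and a woman who conceives on DTG + FTC has been exposed before any switch. The 28% counts all women in both arms; in the DTG + FTC arm alone it would be 28% of 92, about 26. Neither figure counts women who also conceive, breastfeed or plan to conceive and whose earlier regimen conflicts with Section 8.6.
- **That the whole of Section 8.6 was written in response to the 2018 signal.** Only the dated paragraph is. For excluding pregnant and breastfeeding women, the section's stated reason is that triple therapy is standard of care, and no history of the switching sentence is shown.

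**Conclusion.** The inconsistency is real, bears on safety, and should be corrected. Section 7.4 permits, for pregnancy-related stops, regimens that Section 8.6 does not, and it makes continued participation depend on a condition that Sections 8.6 and 10.1.2 do not contain. The regimen conflict affects only women in the DTG + FTC arm who stop for one of these reasons and whose previous regimen contained dolutegravir or, for pregnancy and breastfeeding, was protease-inhibitor dual therapy. The protocol does not give their number, and it may be small or zero. The statistical effect is likewise limited: about 1.1 percentage points per woman under the assumptions shown, in a situation that should be uncommon. The conclusion rests on the wording alone and takes no view on which clinical rule is right.

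**What to change.** Reconcile Section 7.4 with Sections 8.6 and 10.1.2:

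- Take the pregnancy, breastfeeding and conception-related stops out of two general sentences in Section 7.4: the choice between the previous regimen and another, and the eligibility-based withdrawal.
- Refer these stops instead to a single pregnancy rule that states the regimen requirement and whether the woman stays in the trial.
- State in Section 8.1.2 whether the sponsor-agreement step applies to control-arm women who are switched under Section 8.6.

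The content of the clinical rule is for the sponsor to decide. The cost is a wording amendment, handled under Section 2.10, with no added patients, visits or tests and no change to the sample size or the analysis.

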## 8. STUDY INTERVENTION

### 8.1 Identity of Investigational Products (treatment)

#### 8.1.1 Experimental Intervention (treatment)

Dolutegravir 50 mg (Tivicay®) is manufactured by ViiV Health Care. It is a round pale yellow tablet to be taken orally once daily with or without food. DTG 50 mg will be administered once daily in combination with FTC for a duration of 48 weeks.

Emtricitabine 200 mg (Emtriva®) is manufactured by Gilead Sciences. It is blue and white capsule to be taken orally once daily with or without food. FTC 200mg will be administered once daily in combination with DTG for a duration of 48 weeks.

Patient-centered monitoring will include reduced immunological and safety blood analyses (CD4 cell count, lipids and glucose, creatine kinase, renal and hepatic function tests) performed at screening and at week 48. In addition, patients will be offered alternative options for the conduction of study visits, venipuncture and drugs delivery at weeks 6, 12 and 36. Participants will be asked to select at least one of the three following strategies:

- Venipuncture for blood analyses: decentralised venipuncture, e.g. at peripheral laboratory near patient's home or place of work, or with general practitioner, versus at their affiliated SHCS site;
- Drug delivery: delivery of ARV drugs/prescription by mail or at a chosen pharmacy versus at their affiliated SHCS site;
- Assessment and clinical interview: phone call with study nurse/physician versus face-to-face at their affiliated SHCS site.

These options will be organized at study site discretion. Table 1 summarises the differences between the monitoring arms and Table 2 lists the different options chosen by each study site.

Table 1: Summary of the differences between standard and patient-centered monitoring arms

| STANDARD MONITORING*                                                                                                                                                    | PATIENT-CENTERED MONITORING*                                                                                                                                                                                         |
|-------------------------------------------------------------------------------------------------------------------------------------------------------------------------|----------------------------------------------------------------------------------------------------------------------------------------------------------------------------------------------------------------------|
| All visits at SHCS center                                                                                                                                               | Weeks 24 and 48 visits at SHCS center                                                                                                                                                                                |
| WHERE                                                                                                                                                            | Weeks 6, 12, 36 according to patient choice (see HOW below)                                                                                                                                                          |
|                                                                                                                                                                         |                                                                                                                                                                                                                      |
| Week 6:
- HIV-RNA measurement only
Weeks 12, 24, 36 and 48 visits:
- Complete blood analysis with HIV-RNA, CD4 count, full blood count, safety serum chemistry | Week 6, 12, 24, 36:
- HIV-RNA measurement only
Week 48:
- Complete blood analysis with HIV-RNA, CD4 count, full blood count, safety serum chemistry                                                         |
| WHAT                                                                                                                                                             |                                                                                                                                                                                                                      |
|                                                                                                                                                                         |                                                                                                                                                                                                                      |
| - Face to face study visit
- Venipuncture with study nurse
- Drug or prescription delivery according to site usual practice                                       | At least one of the following options:
- Visits: Phone call versus at SHCS center
- Venipuncture: peripheral versus at SHCS center
- Delivery of drugs: by mail or at chosen pharmacy versus at SHCS center |
| HOW                                                                                                                                                              |                                                                                                                                                                                                                      |
|                                                                                                                                                                         |                                                                                                                                                                                                                      |

\* No differences for screening and baseline visit

Table 2: Patient-centered care arm options available at each study site

|                   | Visit      | Laboratory                                                                                                                                                          | Study drug                                                                                                  |
|-------------------|------------|---------------------------------------------------------------------------------------------------------------------------------------------------------------------|-------------------------------------------------------------------------------------------------------------|
| Geneva     | Phone call | - Venipuncture at Dianalabs
- HIV RNA, CD4 and storage at HUG                                                                                                    | DHL (address chosen by the patient)                                                                         |
| Lausanne   | Phone call | - Venipuncture at La Source
- Storage at CHUV                                                                                                                    | Decentralized pharmacy (chosen by the patient)
Labels will be attached to the IMP bottles by the patient |
| Neuchâtel  | Phone call | - Venipuncture at GP office
- Storage at CHUV                                                                                                                    | Decentralized pharmacy (chosen by the patient)
Labels will be attached to the IMP bottles by the patient |
| Lugano     | Phone call | Not available                                                                                                                                                       | La Poste (address chosen by the patient)                                                                    |
| Zurich     | Phone call | - Venipuncture at GP office
- All analyses at USZ laboratory

Not feasible for patients on DTG/metformin
Not feasible for patients new to DTG at week 6 | Decentralized pharmacy (chosen by the patient)
Labels will be attached to IMP bottles by the patient     |
| Bern       | Phone call | - Venipuncture at GP office
- Analyses at Inselspital                                                                                                            | La Poste (address chosen by the patient)                                                                    |
| St. Gallen | Phone call | - Venipuncture at GP office
- Analyses at Kantonsspital and at peripheral lab                                                                                    | La Poste (address chosen by the patient)                                                                    |
| Basel      | Phone call | - Venipuncture at GP office
- Analyses at Universitätsspital                                                                                                     | La Poste (address chosen by the patient)                                                                    |

Patients will also have the opportunity to change or give their opinion on the alternative option chosen if they find it non convenient during the study. Changes will be possible at week 24; satisfaction will be assessed at week 12, 36 and 48.

